**Fig. 1 Fig1:**
[figure not shown]
A visual representation of the computational workflow of the experiment

### Protocol

The study adopts a randomized pretest–posttest control group design with two parallel conditions. Participants are university students accessing the UPCS who report experiencing anxiety and/or stress and meet the eligibility criteria. After a structured screening interview, eligible students provide written informed consent and are then allocated to either the experimental group or the control group through a randomization procedure (Fig. 2). Randomization was performed using Sealed Envelope software with variable block sizes, stratified by gender and site. The experimental group receives a standard psychological counseling program complemented by immersive VR modules, whereas the control group will receive the counseling program only. Participants complete the same set of standardized measures at pretest (before the intervention) and posttest (after the intervention) to allow for within-group and between-group comparisons over time (Fig. 2).

**Fig. 2 Fig2:**
[figure not shown]
Workflow of the randomized controlled trial

The study schedule and assessments are described in detail in Table 1 in accordance with the SPIRIT (Standard Protocol Items: Recommendations for Intervention Trials) guidelines. The completed SPIRIT checklist is provided as Supplementary Material (Table S1).

**Table 1 Tab1:** SPIRIT schedule

Study period	Enrolment	Allocation	Week 1 (T0)	Week 2	Week 3	Week 4 (T1)	T2 (3-mo FU)
ENROLMENT							
Eligibility screen (structured interview)	✓						
Informed consent	✓						
Baseline demographics / clinical info	✓						
ALLOCATION							
Randomization (1:1)		✓					
INTERVENTIONS							
VR-ERP (experimental arm)			✓	✓	✓	✓	
VR-ACT (experimental arm)			✓	✓	✓	✓	
Control arm: counseling only			✓	✓	✓	✓	
ASSESSMENTS							
Demographics and academic data	✓						
PRPSA	✓					✓	✓
STAI-Y State	✓					✓	✓
STAI-Y Trait	✓					✓	✓
Physiological recording (EmbracePlus) • Heart rate (HR); • Heart rate variability (HRV); • Electrodermal activity (EDA); • Skin temperature; • Movement and activity levels.			✓	✓	✓	✓	
Adverse events / discomfort			✓	✓	✓	✓	
Withdrawal	✓	✓	✓	✓	✓	✓	✓

### Interventions

#### Participants

Participants in the control group do not receive VR training but follow the same assessment schedule as the experimental group. Specifically, they complete baseline (T0), post-intervention (T1), and follow-up (T2) evaluations using the same psychological measures. This design allows comparison between intervention and control conditions, thereby isolating the effects of VR training from potential confounding factors such as time and repeated testing effects.

The experimental intervention includes two distinct VR-based training components: (A) VR-ERP, which gradually exposes students to anxiety-provoking situations to prevent avoidance responses, and (B) VR-ACT training, which provides consistent mindfulness practice aimed at enhancing psychological flexibility and value-oriented behaviors. After completing VR-ACT training, participants in the experimental group proceed to a standard counseling intervention.

#### Control arm – counseling program

Standard counseling sessions are conducted by a psychotherapist for five consecutive weeks, consisting of 60-minute individual sessions. Sessions are structured as follows:

Session one: The therapist builds the therapeutic alliance and promotes acceptance and psychological flexibility processes within a non-judgmental and safe space. The session includes psychoeducation on the function of social anxiety and the distinction between avoidance and value-oriented behaviors.

Sessions two to four: The psychotherapist promotes self-as-context, cognitive defusion and restructuring, contact with the present moment, values clarification, acceptance, and committed action to transform the relationship with difficult emotions and to enhance behavioral activation and emotion regulation. Sessions include an individualized case formulation and between-session homework assignments.

Session five: The psychotherapist focuses on consolidation and relapse prevention and administers the post-intervention assessment (T1).

Follow-up session: Participants in both conditions complete follow-up assessments 3 months post-intervention to evaluate the stability of treatment effects and detect delayed or emerging improvements. These structured touchpoints also allow counselors to identify residual or emerging difficulties, thereby strengthening ecological validity and clinical utility.

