## Method

### Aim

We adopt a two-arm randomized controlled trial (RCT) design to investigate whether VR-delivered controlled exposure can complement standard psychological counseling in addressing PSA and general anxiety symptoms among students accessing the UPCS. The findings are expected to provide evidence regarding the effectiveness of integrating VR-based exposure as an adjunct to Exposure and Response Prevention–Acceptance and Commitment Therapy (ERP-ACT) within counseling to manage anxiety and stress in university students.

It is hypothesized that:

Primary Outcome - Students receiving brief psychological counseling supported by ERP and ACT training combined with VR-based exposure exhibit significantly greater reductions in PSA and anxiety levels from baseline (T0) to post-intervention (T1), compared with students receiving standard psychological counseling alone.Secondary Outcome - The two VR components (ERP and ACT) are expected to exert differential effects. Specifically, the relaxation modules should primarily reduce physical tension and physiological arousal, whereas the immersive exposure modules should mainly target the psychological aspects of public speaking, leading to lower fear and reduced perceived mental effort during performance-related scenarios. Physiological data are continuously recorded during each intervention session to assess patterns of arousal and recovery and to examine whether VR-supported counseling is associated with different within-session responses compared with counseling alone.Other Pre-specified Outcome - These benefits are expected to be maintained over time; therefore, students in the VR-ERP and VR-ACT training conditions are expected to continue to exhibit better outcomes at the 3-months follow-up assessment (T2), compared with students receiving standard counseling alone.

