### Design and setting of the study

The study is a two-arm randomized controlled trial with parallel, independent experimental and control groups. Both groups undergo a brief standard counseling program consisting of five individual sessions delivered by trained clinicians within the UPCS. The experimental group receives the same brief standard counseling intervention, complemented by two immersive VR modules delivered through 360° video-based scenarios: (a) a VR–Exposure and Response Prevention (VR-ERP) component providing graded and controlled exposure to anxiety-provoking public-speaking situations, and (b) a VR-Acceptance and Commitment Training (VR-ACT) component offering an ACT-based mindfulness training aimed at down-regulating physiological arousal and enhancing adaptive coping. The control group receives the standard counseling protocol only.

Psychological assessments are conducted at baseline (T0), post-treatment (T1), and at follow-up (T2), allowing evaluation of change over time and between-group differences. Physiological parameters are continuously recorded during each session to capture objective indices of arousal and recovery alongside self-report outcomes. This design enabled testing whether adding immersive, VR experiences to routine counseling provides benefits beyond standard care alone.

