### Participants and recruitment

Potential participants are identified among university students who contact the UPCS. Each student undergoes a structured screening interview conducted by a research psychologist. During this interview, the aims and procedures of the study are explained, questions are addressed, and the student’s eligibility is assessed. The screening serves to rule out conditions requiring immediate or specialized care; in such cases, students are referred to the appropriate clinical services within or outside the university, in accordance with standard UPCS referral pathways.

Eligible participants are university students aged 18 years or older who seek counseling at the UPCS and report clinically relevant anxiety in performance-related contexts, particularly public speaking.

Inclusion criteria are: (a) current enrolment at the university; (b) request for psychological counseling at the UPCS; (c) age ≥ 18 years; (d) fluency in Italian; (e) provision of written informed consent; and (f) at least moderate levels of anxiety and perceived stress as indicated by standardized measures, specifically, Personal Report of Public Speaking Anxiety (PRPSA) scores between 85 and 110 and State-Trait Anxiety Inventory (STAI) scores between 35 and 50.

Exclusion criteria are: (a) current psychotic disorder; (b) acute suicidal ideation or behavior; (c) severe substance dependence; (d) severe sensory or motor impairments that could interfere with the safe use of VR equipment; (e) inability to attend the planned sessions; and (f) concurrent participation in other specialized psychotherapy programs.

After completion of the screening interview, participants are randomized (1:1) to the experimental (counseling + VR) or control (counseling only) group using a computer-generated randomization sequence. Allocation is concealed using sequentially numbered, opaque, sealed envelopes or a password-protected electronic system, which is accessed only after participant enrollment and completion of baseline (T0) measures.

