### Ethics and privacy

Written informed consent will be obtained from participants prior to study participation, following a comprehensive explanation of the study aims, procedures, and the provision of written information. The study received ethical approval (No. 112518/2025) from the Institutional Review Board Committee (IRBC) of the University of Calabria and is registered with the ClinicalTrials.gov (NCT07351409) on January 16, 2026. Data will be collected through a secure, encrypted digital platform and stored on institutional servers in compliance with General Data Protection Regulation (GDPR) and institutional ethics guidelines. All datasets used for analysis will be fully de-identified using unique participant identification codes.

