#### Psychological assessment

The protocol involves the assessment of participants through the administration of standardized self-report psychological tests designed to evaluate levels of public speaking anxiety and state and trait anxiety levels.

The instruments are:

The Italian version of the *Personal Report of Public Speaking Anxiety* (PRPSA) [23] is a self-report questionnaire designed to measure the level of anxiety individuals experience when speaking in public. The scale assesses multiple dimensions of public speaking anxiety, including cognitive, physiological, and behavioral components, capturing both anticipatory anxiety and anxiety during performance. The PRPSA consists of 34 items, each rated on a 5-point Likert scale (1 = strongly disagree to 5 = strongly agree). Items reflect feelings of tension, nervousness, and physiological arousal (e.g., “My hands tremble when I try to handle objects on the podium”), as well as negative self-appraisal and fear of audience evaluation. Total scores range from 34 to 170, with higher scores indicating greater levels of public speaking anxiety. Conventionally, scores above 131 suggest high anxiety, scores between 98 and 131 indicate moderate anxiety, and scores below 98 indicate low anxiety. The Italian version maintains strong psychometric properties, with high internal consistency (Cronbach’s α > 0.90) and good test–retest reliability. It has been validated for use among university students and adults, proving useful in both clinical and research contexts, examining performance-related social anxiety and communication apprehension.The Italian version of the *State-Trait Anxiety Inventory*,* Form Y* (STAI) [24, 25] was adopted to measure two distinct dimensions of anxiety: (i) State Anxiety (S-Anxiety), a temporary emotional condition characterized by feelings of tension, apprehension, and heightened autonomic nervous system activity, reflecting how the respondent feels at the present moment; and (ii) Trait Anxiety (T-Anxiety), a relatively stable disposition to perceive situations as threatening and to respond with anxiety across time and contexts. Each subscale consists of 20 items, rated on a 4-point Likert scale (ranging from 1 = almost never to 4 = almost always for trait anxiety, and 1 = not at all to 4 = very much so for state anxiety). Scores range from 20 to 80 for each subscale, with higher scores indicating greater anxiety levels. The Italian adaptation has demonstrated good psychometric properties, including high internal consistency (Cronbach’s α typically between 0.86 and 0.95) and construct validity consistent with the original instrument, making it one of the most widely used anxiety measures in both clinical and research settings in Italy.

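### The treating psychotherapist administers the self-report primary outcomes at T1 within the final counseling session, so arm-related reporting can enter the T0-to-T1 contrast

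*Protocol article*

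**What the plan says.** The section on the control-arm counseling program describes session five in these words: "The psychotherapist focuses on consolidation and relapse prevention and administers the post-intervention assessment (T1". The same section says who provides the treatment: "Standard counseling sessions are conducted by a psychotherapist for five consecutive weeks". The administrator of T1 is therefore a provider of the treatment under test.

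The sentence stands under the control-arm heading, but the design section extends it to both arms: "Both groups undergo a brief standard counseling program consisting of five individual sessions delivered by trained clinicians within the UPCS", and "The experimental group receives the same brief standard counseling intervention, complemented by two immersive VR modules".

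The Aim section sets the primary hypothesis as "significantly greater reductions in PSA and anxiety levels from baseline (T0) to post-intervention (T1", compared between arms. The psychological instruments are PRPSA and the two STAI-Y scales, all self-report. The psychological assessment section describes STAI-State as "reflecting how the respondent feels at the present moment". STAI-Trait is described as a stable disposition, and PRPSA as a measure of speaking anxiety.

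On baseline, Participants and recruitment describes a "structured screening interview conducted by a research psychologist" and says that allocation is accessed only after the T0 measures are complete. On data capture, Ethics and privacy says: "Data will be collected through a secure, encrypted digital platform". No section names an independent or blinded administrator for T1.

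**The concern.** Participants cannot be blinded to VR, so their answers at T1 are already open to expectation. The plan adds a second route that it does not need: the answers are given to the person who delivered the therapy, in the session devoted to consolidating its gains. Students may understate their anxiety to their own therapist. If that tendency differs between arms, the difference counts as treatment effect.

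There are reasons why it might differ. Experimental students have a novel treatment to credit, and each VR exposure session is followed by a supportive debriefing. STAI-State has a further weakness, because a momentary measure taken in or just after a session partly measures that session.

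The primary between-arm contrast is at stake. The models in Statistical analyses cannot separate a reporting difference from a true difference, and a larger sample does not help.

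**Working it through.** **1. What cancels and what does not.** Let the true mean change from T0 to T1 be D_E in the experimental arm and D_C in the control arm. Let r_E and r_C be the mean reporting shifts caused by answering to the therapist. The observed contrast is

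(D_E + r_E) − (D_C + r_C) = (D_E − D_C) + (r_E − r_C).

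If r_E = r_C, the second term is zero and the contrast is unbiased. Baseline cannot depend on the arm, because T0 precedes the opening of allocation. T1 is given with the arm known to the participant and very probably to the therapist. So any difference r_E − r_C arises at T1 and enters the contrast in full.

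**2. Does the therapist know the arm?** The article does not say. The Discussion describes VR exposure as embedded in an ongoing counseling relationship, which makes blinding of the therapist implausible. This is an inference.

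**3. When is T1?** The sections disagree:

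| Section | Timing of T1 |
|---|---|
| Control arm – counseling program | Session five of five weekly sessions |
| Psychological assessment | End of a 4-week intervention period |
| Physiological assessment | Session 4 |
| Table 1 (SPIRIT schedule) | Week 4 |

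This matters for STAI-State.
- If T1 is in session five, Table 1 shows VR only through Week 4. A same-day VR effect is then unlikely, and the session effect is broadly common to both arms.
- If T1 is in Week 4, Table 1 puts both VR modules in the same column. VR sessions end in a relaxation phase, and experimental participants go on from VR-ACT to counseling. STAI-State could then be taken soon after a calming exercise in one arm only. The table shows the same week, not the same day, but no stated rule prevents it.

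**4. The plan's own figure.** Inputs from Sample size: d = 0.75, two-sided α = 0.05, power 0.80. The noncentral t has df = 2n − 2 and noncentrality d·√(n/2). With n = 29: df = 56, noncentrality 0.75 × √14.5 = 2.856, power 0.801. With n = 28 the power is 0.787. So 29 per group is reproduced. Allowing for 20% dropout, 29 / 0.8 = 36.25, against 36 stated. Nothing in this point changes the sample size.

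**5. Illustration of sensitivity.** The documents give no size for r_E − r_C. Assume a shift of b standard deviations of the change score and no true effect. The same test then has noncentrality b·√(n/2), and its two-sided rejection rates are:

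| Assumed b | b / 0.75 | 29 per group | 36 per group |
|---|---|---|---|
| 0 | 0% | 5.0% | 5.0% |
| 0.1 | 13% | 6.6% | 7.0% |
| 0.2 | 27% | 11.6% | 13.3% |
| 0.3 | 40% | 20.2% | 24.1% |

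The values of b are free assumptions. The t-test is the planning test, while the primary analysis is a mixed model. The table shows only that a modest differential shift would matter and that more participants would make false rejection more likely.

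**The case against.** The strongest defense is that the design is symmetric. Both arms have the same counseling and the same assessment schedule, so pressure from the therapist, or a calming session, that acts equally drops out. That stands, and bias requires a differential effect that the documents do not demonstrate. What remains is that T1 is collected under conditions where a differential is plausible.

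Novelty and extra contact also act through the participant's own awareness of the arm, and would persist with private completion. This stands too. It would be wrong to infer that the bias is wholly avoidable, since only the part tied to the therapist and the session can be removed.

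The word administers may mean only that the forms are scheduled at that visit, with the student entering answers alone on the platform. The article neither says this nor rules it out. As written, it assigns the task to the therapist, and the mention of a platform does not take it away. This is a stated procedure, not a detail left to a fuller document.

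Two stronger readings are not supported:
- A reader might infer that the setting changes between T0 and T1 because a research psychologist conducts the screening. The article assigns that person the interview only, and does not say who administers the T0 questionnaires or where.
- A reader might extend the momentary-state argument to all three scales. It applies to STAI-State only.

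**Conclusion.** The point holds in a limited form. The plan has a treatment provider administer the self-report primary outcomes at T1 in the final counseling session, in both arms. Because baseline precedes allocation and T1 does not, any arm-related reporting to the therapist biases the primary contrast. For STAI-State there is an additional route through same-day session content, which differs by arm only if T1 falls beside VR sessions in Week 4.

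The conclusion rests on one inference (the therapist knows the arm) and one plausible but unproven condition (the reporting shift differs between arms). The size cannot be estimated from the document. The rejection rates of 6.6% to 20.2% at 29 per group follow from assumed shifts of 0.1 to 0.3 SD and must not be read as this trial's error rate. The point does not invalidate the trial. It identifies an avoidable weakness in how the primary outcome is collected, which analysis cannot repair afterwards.

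**What to change.** Reconcile the timing of T1 across the counseling program, Psychological assessment, Physiological assessment and Table 1 before anything else.

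Then replace the session-five clause with a statement that:
- T1 questionnaires are completed by the participant alone on the digital platform already planned;
- completion is after the last session, on a day (or within a short fixed window) with no counseling or VR content;
- the procedure is the same in both arms and the mode is the same as at T0;
- the treating therapist neither administers the questionnaires nor sees the answers until entry is locked.

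Apply the same procedure at T2 for consistency; the article does not say that the therapist administers T2.

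Completion should not simply be moved to just before the counseling in session five. That would measure the outcome before the fifth session, although T1 is defined as post-treatment.

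The cost is a few sentences of protocol text, with no extra staff and no change to the sample size or treatment. The downside is a few more late or missing forms than with in-session completion, which automatic reminders can limit. Participants remain unblinded, so some reporting bias will persist.

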### Sample size

A priori sample-size estimation is conducted to determine the number of participants required to detect the expected effects of the VR-based exposure intervention on the primary outcome measures. Evidence from a systematic review [21], which examined virtual reality–based interventions targeting public-speaking anxiety in student populations, indicates that VR exposure procedures typically yield moderate-to-large reductions in anxiety symptoms compared with control or baseline conditions. Reported effects across the studies reviewed are consistent with the magnitude commonly observed in the broader VRET literature, supporting the assumption of a moderately large effect size for the planned between-group comparison.

Based on this evidence, we adopt an expected effect size of Cohen’s d = 0.75 for the between-group differences in change scores from baseline to post-intervention between the VR exposure and control groups. A power analysis conducted using G*Power 3.1 (two-tailed independent-measures t-test, α = 0.05, power = 0.80) indicated that 29 participants per group would be required to detect an effect of this magnitude.

To ensure adequate statistical power after accounting for participant attrition, commonly estimated at 15%-20% in VR-based intervention studies, we plan for an upper-bound dropout rate of 20%. Accordingly, the required number of participants is adjusted to 36 participants per group, resulting in a total target sample of 72 participants [22]. This sample size is expected to provide sufficient statistical sensitivity to detect clinically meaningful effects of the VR intervention while remaining feasible for a single-site randomized controlled trial.

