
The psychological tests used to assess the students will be administered at baseline (T0), post-treatment (T1, at the end of the 4-week intervention period), and after 3 months (T2, follow-up).

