#### Physiological assessment

The EmbracePlus wristband is a research-grade, wrist-worn wearable device designed to continuously monitor a range of physiological parameters, providing real-time access to raw sensor data suited for scientific, clinical, and real-world studies. Its built-in sensors include photoplethysmography (PPG) for blood volume pulse (BVP), from which heart rate (HR), inter-beat interval (IBI), and heart rate variability (HRV) are derived, electrodermal activity (EDA or skin conductance) as an index of autonomic arousal, a 3-axis accelerometer to track motion and activity, and a peripheral skin-temperature sensor. The device samples EDA at 4 Hz and PPG at 64 Hz, and it has demonstrated high correlations with clinical-grade equipment for HR and HRV under controlled conditions (though less so for EDA under movement) [26]. Thanks to its wrist-worn design, on-board data storage, and Bluetooth syncing capabilities, the EmbracePlus enables extended ambulatory monitoring of physiological responses in naturalistic settings, enabling studies of stress, emotion, cognitive load, and behavioral states in real time. Data were collected during four intervention sessions, from Session 1 (T0; baseline) to Session 4 (T1), corresponding to the end of the 4-week intervention period.

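### The primary T1 assessment is scheduled as an activity of counseling Session five and no other route is stated, so its collection depends on attending the last session

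*Protocol article*

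**What the plan says.** Under Control arm – counseling program, the protocol article describes Session five as follows: "The psychotherapist focuses on consolidation and relapse prevention and administers the post-intervention assessment (T1". The same section sets the length of the program: "Standard counseling sessions are conducted by a psychotherapist for five consecutive weeks".

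The text stands under the control-arm heading, but it reaches both arms. Design and setting of the study states: "Both groups undergo a brief standard counseling program consisting of five individual sessions". The Participants paragraph under Interventions puts both groups on the same assessment schedule.

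Other sections time T1 differently. Psychological assessment has "post-treatment (T1, at the end of the 4-week intervention period". Physiological assessment describes recording "from Session 1 (T0; baseline) to Session 4 (T1), corresponding to the end of the 4-week intervention period". Table 1 marks PRPSA and both STAI scales in the Week 4 (T1) column and has no column for a fifth week.

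The primary measures are described as "administration of standardized self-report psychological tests". On capture, Ethics and privacy states: "Data will be collected through a secure, encrypted digital platform". The withdrawal reasons in Participants and recruitment do not name a missed counseling session. Statistical analyses relies on linear mixed models over T0, T1 and T2, with multiple imputation as a sensitivity check if dropout looks non-random.

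**The concern.** The primary hypothesis concerns change from T0 to T1. If the T1 forms are handed out as part of the last treatment session, stopping treatment and losing the outcome become the same event. A student can miss sessions and remain in the trial, and the article gives no route by which that student's T1 would be obtained. A student who postpones sessions could be measured later than others.

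Two things are at stake. First, T1 would be observed mainly in students who complete counseling. If non-attendance is related to how much a student benefits, and differs between arms, the comparison of those observed is biased. Second, each avoidable gap costs power in a trial of 72. The coupling also looks unnecessary, because the forms are self-report and a digital collection platform already exists.

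**Working it through.** **1. Does the stated procedure tie T1 to attendance?**

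- How T1 is administered is described once, in Session five, by the therapist.
- Both arms have the same five sessions and the same assessment schedule.
- A missed session is not, by name, a reason for withdrawal.
- The article neither states nor excludes a make-up route.

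So, following the text, a retained student who misses Session five has no stated route to T1. That is weaker than saying the student cannot be assessed.

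**2. When is T1?** With one session a week from week 1, Session five falls in week 5. Psychological assessment and Table 1 put T1 at week 4, and Physiological assessment equates it with Session 4. These places differ by one session, or about a week, so T1 has no single calendar anchor.

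**3. The plan's own sample size.** Inputs from Sample size: d = 0.75, two-sided α = 0.05, power 0.80, independent t-test, 20% dropout.

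- Noncentral t: n = 28.90, so 29 per arm, with power 0.801. This reproduces the plan.
- Dropout: 29 / (1 − 0.20) = 36.25. The plan uses 36, which leaves 36 × 0.80 = 28.8 and power 0.799. The rounding is immaterial.

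**4. Possible bias (illustration).** Let p be the share of an arm without T1 and g the amount by which those students improve less than attenders. The full-arm mean improvement is then the attenders' mean minus p × g, so an attenders-only contrast is shifted by (p_VR − p_control) × g when g is the same in both arms. None of these inputs is in the document.

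| Assumed p, VR / control | Assumed g | Shift in favour of VR |
|---|---|---|
| 25% / 15% | 8 points | 0.10 × 8 = 0.8 points |
| 30% / 10% | 12 points | 0.20 × 12 = 2.4 points |
| equal | any | 0 |

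At an assumed SD of change of 12, 2.4 points is 2.4 / 12 = 0.2 SD. If non-attendance were higher in the control arm, the sign would reverse. The formula describes attenders only; the planned mixed model also uses T0 and any T2.

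**5. Possible power effect (illustration).** Let x be an additional share of retained students without T1, beyond the 20%. Complete-case t-test, n = 36 × 0.80 × (1 − x):

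| x | n per arm | Power | Enrolled per arm to keep 29 |
|---|---|---|---|
| 0 | 28.8 | 0.799 | 37 |
| 5% | 27.36 | 0.777 | 39 |
| 10% | 25.92 | 0.754 | 41 |
| 15% | 24.48 | 0.729 | 43 |
| 20% | 23.04 | 0.702 | 46 |

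In the other direction, suppose half of the 36 − 29 = 7 losses allowed per arm could be recovered. Then n = 29 + 3.5 = 32.5 and power rises from 0.801 to 0.845; with all 36 it would be 0.881.

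**The case against.** The strongest reply is that assessing at the final session is ordinary practice, and that make-up contacts and windows are details a journal article leaves to the full protocol. This is right as far as it goes. A reader might infer that a student who misses Session five yields no primary outcome. The article does not say so, and its other sections tie T1 to week 4 rather than to Session five. What stands is that the procedure it does state makes T1 part of a treatment session.

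A reader might also infer that missingness will differ by arm because VR adds burden. Session five is common to both arms. The VR phases total about 15 minutes, and Table 1 lists them in the same weeks 1 to 4 as counseling. The Discussion expects the high commitment required to raise attrition, but not in one arm specifically. A difference is plausible and not shown.

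Nor is it correct that the model has only T0 for such a student. T2 is a separate 3-month assessment and enters the model if obtained. The limit is that the model is valid only under missing at random, and multiple imputation normally rests on the same assumption. Stopping because counseling is not helping could breach it.

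Finally, the power gain should not be read as available. Sample size describes its allowance as "participant attrition, commonly estimated at 15%-20% in VR-based intervention studies" and takes 20% as an upper bound. That includes students who withdraw, whose T1 a new procedure may not recover. If the allowance already covers missed T1 forms, planned power is unchanged.

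**Conclusion.** The point holds as a design risk. The article schedules the primary T1 assessment inside counseling Session five and states no alternative, so its collection depends on attendance at the last session, and T1 may be missing or late for a retained student who skips or postpones sessions.

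The document does not establish how often this would happen, whether it would differ by arm, or that the planned analysis would be biased. The 0.8 to 2.4 point shifts rest on assumed rates, gaps and SD, and apply to an attenders-only contrast. The power figures (0.78 to 0.70 with 5% to 20% extra missing T1, or a rise from 0.80 to 0.85 with half the allowed losses recovered) likewise rest on assumed shares. The sample-size calculation itself reproduces and is not in question.

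The conflict over T1 timing (week 4 or Session 4 against Session five) is explicit in the text and needs no assumption. The change is worth making because it is cheap and removes an avoidable link between stopping treatment and losing the outcome.

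**What to change.** Amend the Session five description so that T1 is not an activity of that session. State instead that PRPSA and STAI at T1 are requested from every randomized student who has not withdrawn, in one pre-specified calendar window that is identical in both arms, whatever sessions were attended, with a reminder. Use the existing digital platform where it allows this; the article does not say whether it can send forms remotely, so the sponsor should confirm that first.

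When setting the window, reconcile Psychological assessment, Physiological assessment and Table 1 with Control arm – counseling program, so that T1 has one definition throughout.

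T2 needs no equivalent change, since it is already a separate 3-month assessment.

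The cost is a scheduled request and a reminder, and less control over the setting in which forms are completed. No treatment content changes. Recruitment is expected to run until December 2026, so an amendment may still benefit students yet to be enrolled.
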